#### Interim analyses {21b}

No interim analyses will be conducted as we do not foresee any potentially serious outcomes.

#### Methods for additional analyses (e.g. subgroup analyses) {20b}

Baseline data will provide cross-sectional results on work status, pain intensity, quality of life, disability, medication use and self-management for the complete PSPS-T2 group and comparisons between possible subgroups. Furthermore, correlation analyses will be performed in order to unravel correlations between the different outcome measures in patients with PSPS-T2, eligible for SCS. Correlation analysis will be performed with Pearson correlation coefficients if the assumption of a linear relation between two variables is met; otherwise, Spearman correlation coefficients will be calculated and tested at alpha < 0.05.

A within trial economic evaluation will be conducted. All costs of all patients will be considered, for the time horizon starting from start of the allocated intervention until the 6-month follow-up period. Intervention costs will be based on the study notes documenting the duration of each session per patient. The valuation of resource use is based on national tariffs. Health outcomes will be expressed in two ways: (1) percentage holistic responders, which is the primary outcome in this trial, and (2) utility using health state values from the general public. The overall result is expressed in an incremental cost effectiveness ratio (ICER, i.e. incremental cost divided by the percentage increment in holistic responders and incremental cost divided by the incremental QALY gained). Differences in cost between both groups will be analysed using generalised linear models. The point estimates of incremental costs and increment health benefits (deterministic analyses) are subject to uncertainty which will be addressed in probabilistic analyses [52]. We will apply nonparametric bootstrapping to test for statistical differences in costs and health benefits to investigate the uncertainty around these outcomes and summarised in cost-effectiveness acceptability curves indicating the likelihood of the intervention to be cost-effective at any willingness-to-pay threshold. Reporting on the results of the health economic evaluation will be in line with the CHEERS II guidelines [53]. Besides the within-trial health economic evaluation, a model-based evaluation will be conducted in order to estimate the expected costs and health outcomes in both intervention groups beyond the follow-up period of the trial. A Markov-model will be developed compliant to the commonly used guidelines [54].

#### Methods in analysis to handle protocol non-adherence and any statistical methods to handle missing data {20c}

Both intention-to-treat as well as per protocol analyses will be conducted to determine whether both definitions of the population will point towards similar results, which could improve robustness of the results. At first, analysis will be performed on data as observed. Hence, intermittent missing is not expected to substantially bias the results. To address possible informative drop-outs, a sensitivity analysis will be performed using multiple imputation, including all available information on background characteristics and outcome. All analysis will be performed in SAS or R.

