#### Sample size {14}

Sample size calculation was performed using the formula for large sample tests for proportions [50] and more specifically to test for equality between the proportion of clinical holistic responders in both interventions. The estimated proportion of clinical holistic responders is estimated at 47.8% in the subthreshold SCS group [51] and assumed to be 12.6% in the BMT group. The latter is an assumption based on the mean of the difference in primary outcome measures from the PROCESS and PROMISE trials at 6 months since no values for clinical holistic responders in BMT are available yet [10, 11]. By assuming an equal allocation, a sample size of 114 participants is needed with 57 participants in each intervention group. This sample size calculation accounts for a 20% loss to follow-up after 6 months and a 12% trial failure rate [51]. Calculations were performed for achieving an 80% power at the 5% level of significance.

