### Statistical methods

#### Statistical methods for primary and secondary outcomes {20a}

Considering the longitudinal data, a generalised estimating equation will be constructed to evaluate and compare therapy effects. The primary outcome will be analysed as the proportion of clinical holistic responders from baseline to 6 months (taking into account the longitudinal nature of the trial) between both groups. Baseline variables will be used as covariates. For secondary outcome measurements, a similar strategy will be applied with longitudinal mixed models. This longitudinal data analysis approach will also be applied for 12 months data. Statistical as well as clinical significant differences will be defined at alpha < 0.05. Furthermore, based on the baseline data, we will determine predictive factors and which subgroup of patients will benefit the most of the treatment. All analysis will be performed in SAS or R.

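### The multiple imputation named for informative drop-out rests, as described, on missing at random, so it does not test drop-out that depends on the unseen 6-month outcome

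*Protocol article*

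**What the plan says.** Section {20a} names the model for the primary outcome: "a generalised estimating equation will be constructed to evaluate and compare therapy effects". No weighting for drop-out is mentioned. Section {20c} then sets the order of work. The first step is "At first, analysis will be performed on data as observed", defended by one sentence: "Hence, intermittent missing is not expected to substantially bias the results". Drop-out is dealt with separately: "To address possible informative drop-outs, a sensitivity analysis will be performed using multiple imputation", and that imputation is described as "including all available information on background characteristics and outcome".

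Three other parts of the article bear on this:

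- **Sample size {14}:** "This sample size calculation accounts for a 20% loss to follow-up after 6 months and a 12% trial failure rate".
- **Blinding {17a}:** patients and treating physicians know the allocation.
- **Assessments {18a}:** the only follow-up before the 6-month endpoint is at 1 month.

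**The concern.** The section names a problem and assigns a method to it, and the two do not match. Drop-out is informative, in the usual sense, when the chance of leaving depends on the outcome that was then not recorded, even after allowing for everything that was. An imputation model made only of recorded background and outcome data assumes the opposite: given those data, patients who left and patients who stayed have the same outcome distribution.

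The sentence of reassurance does not close the gap. It concerns intermittent missingness, whereas a patient lost before 6 months has no primary outcome at all, and the plan allows for one in five being lost. Because patients know their treatment, leaving may well be related to how they are doing.

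At stake is the size of the responder difference. It is the primary result, and it is also the denominator of the cost per additional responder in section {20b}. If drop-out depends on the unseen outcome, the planned sensitivity analysis may agree closely with the main analysis without having tested that possibility.

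**Working it through.** **1. What each analysis assumes**

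| Analysis | Drop-out under which it is valid |
|---|---|
| Unweighted GEE on observed data ({20a}, {20c}) | Completely random, or dependent only on covariates in the model |
| Multiple imputation from recorded background and outcome data ({20c}) | Missing at random: may depend on recorded data, including the 1-month outcome |
| Drop-out that depends on the unrecorded 6-month outcome | Covered by neither as described |

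The second assumption is weaker than the first, so the imputation does add something. It stops short of the case it is named for.

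**2. Inputs for the size**

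Section {14} gives the planning values: "The estimated proportion of clinical holistic responders is estimated at 47.8% in the subthreshold SCS group" and "assumed to be 12.6% in the BMT group". The planned difference is 47.8 − 12.6 = 35.2 points. Two assumptions are needed. The planning rates are taken as the rates among patients observed at 6 months, and the 20% loss is taken to apply to each arm. The article states neither.

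**3. Mixture arithmetic**

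Rate in all randomised = 0.8 × observed rate + 0.2 × rate in drop-outs.

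| Assumption about drop-outs | SCS | BMT | Difference |
|---|---|---|---|
| Same as those observed, both arms | 47.8% | 12.6% | 35.2 points |
| All non-responders, both arms | 0.8 × 47.8 = 38.2% | 0.8 × 12.6 = 10.1% | 28.2 points |
| SCS drop-outs non-responders, BMT drop-outs as observed | 38.2% | 12.6% | 25.6 points |
| SCS drop-outs at the BMT rate, BMT drop-outs as observed | 38.2 + 0.2 × 12.6 = 40.8% | 12.6% | 28.2 points |
| SCS drop-outs as observed, BMT drop-outs non-responders | 47.8% | 10.1% | 37.7 points |

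Differences are taken before rounding. In the last row the difference is larger than the one observed, so the direction is not fixed.

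**4. A delta scale for the SCS arm**

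Let the log-odds of response in SCS drop-outs be shifted by delta from those observed, with BMT unchanged. The difference is 35.2 points at delta 0, 32.8 at −0.5, 30.7 at −1 and 27.8 at −2. The deltas are assumptions, since the article gives none.

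**5. Does imputation remove the bias?**

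This was checked by simulation with 400,000 patients per arm, 6-month rates of 47.8% and 12.6%, and an assumed latent correlation of 0.6 between the 1-month and 6-month outcomes. BMT loss was 20% at random throughout. Missing 6-month outcomes were imputed within arm from the 1-month response.

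| Drop-out in the SCS arm (assumed) | True difference | Observed data | Imputation under missing at random |
|---|---|---|---|
| (a) 20%, completely random | 0.351 | 0.351 | 0.351 |
| (b) Lost: 30% of 1-month non-responders, 5% of responders | 0.353 | 0.384 | 0.353 |
| (c) Lost: 34% of 6-month non-responders, 5% of responders | 0.352 | 0.442 | 0.427 |

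The observed-data figure in (c) can be checked by hand. The SCS rate among those who stay is 0.478 × 0.95 / (0.478 × 0.95 + 0.522 × 0.66) = 0.454 / 0.799 = 0.569, and 0.569 − 0.126 = 0.443. In (b) imputation removes all the bias. In (c) it removes 0.442 − 0.427 = 1.5 of 0.442 − 0.352 = 9.0 points.

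**6. Would the conclusion be lost?**

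With all 57 per arm counted and a two-sided 5% test, power is about 95% at 38.2% against 10.1%, and about 89% at 38.2% against 12.6%. Under these scenarios the trial would still be likely to show a difference.

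**The case against.** The article never uses the phrase missing at random, and it does not say whether imputation is done within arm. Multiple imputation is also the usual vehicle for delta-adjusted and reference-based analyses, and an analysis plan that is not shown may specify one. This stands in part. Absent detail is not the fault. The fault is that the one description given, an imputation model made of recorded data, is presented as the answer to informative drop-out. If the authors meant the word loosely, as drop-out related to the outcome history, then a GEE followed by imputation is a coherent sequence and only the wording needs correcting.

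Some stronger readings are tempting, and the documents do not support them:

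- **A reader might infer that neither analysis gives any protection, or that the imputation merely repeats the GEE's assumption.** It does not. Imputation that uses the 1-month outcome relaxes that assumption and removed all the bias in scenario (b). Early disappointment in an open-label trial may be partly of that kind.
- **A reader might infer a bias of 7 to 10 points in favour of SCS.** The upper figure comes from failing the SCS drop-outs alone (35.2 − 25.6 = 9.6). The same rule in both arms gives 7.0 points, and loss of BMT non-responders pulls the other way. The offer to switch groups after the 6-month assessment also gives dissatisfied patients a reason to stay until then.
- **A reader might infer that the imputed result is to be presented as proof of robustness.** Section {20c} uses that idea for agreement between the intention-to-treat and per-protocol analyses, not for the imputation.
- **A reader might conclude that imputation must replace the GEE as the main analysis.** That is a matter of preference and does not follow from this point.

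**Conclusion.** The point holds in limited form. As described, the analysis assigned to informative drop-out assumes missing at random. It improves on the observed-data GEE for drop-out related to recorded data, and leaves drop-out that depends on the unrecorded 6-month outcome untested. The stated reassurance does not cover that case.

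Under the assumptions in the working, counting missing patients as non-responders lowers the difference by 7.0 points when applied to both arms and by 9.6 when applied to SCS alone; applied to BMT alone it raises it by 2.5. These are illustrations, not estimates: the drop-out patterns, the correlation of 0.6 and the deltas are all assumed. The main risk is a misstated effect size rather than a lost conclusion. The change is worth making before the data are analysed, but the trial's validity does not turn on it.

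**What to change.** Keep the planned GEE. In section {20c}, describe the multiple imputation as an analysis under missing at random and state that the imputation model includes the 1-month outcomes. Replace or supplement the sentence on intermittent gaps with one on loss before 6 months.

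Then add, as the sensitivity analysis for informative drop-out:

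1. Delta-adjusted or reference-based imputation, with the departure varied separately in SCS and BMT, and a tipping point reported: the combinations of departures at which the conclusion would change.
2. Missing counted as non-responder in both arms.

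No new data are needed. The cost is a little more programming, and the reported range of effects may include smaller differences than the main analysis shows.

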#### Plans to give access to the full protocol, participant level-data and statistical code {31c}

After finalising the project, access restrictions will be applied to the pseudonymised data and will be specified in a data use agreement containing following elements: evaluation of the re-use request by ethical committee, non-disclosure agreement and warranties for safely storage of data.

### Oversight and monitoring

#### Composition of the coordinating centre and trial steering committee {5d}

The steering committee is the main decision-making and steering body of the project. The steering committee consists out of [name], [name] and [name] The steering committee organised a kick-off meeting at the start of the project to establish common working procedures. The main tasks of the steering committee are as follows: (1) agree on common working procedures and management policies, (2) monitor overall progress and follow-up of deliverables, (3) decisions on major changes to the work programme and (4) conflict handling. The steering committee is also responsible for assuring the quality of the workflow and project implementation, considering the available resources. The steering committee will further assemble meetings at least every 6 months. Additional teleconferences can be organised ad hoc in case of urgent issues.

The local principal investigators in the recruiting centres are responsible for patient recruitment and form the TRADITION consortium, together with the steering committee members.

The valorisation board, in which relevant stakeholders take part, will be asked to actively contribute to implementation of the study findings, and any difficulties experienced during the implementation process will be discussed. The researchers will support the stakeholders with the implementation process. In addition, the valorisation board will prepare and guide the full utilisation process in the period following the completion of the research project (after-trajectory), together with the steering committee.

#### Composition of the data monitoring committee, its role and reporting structure {21a}

The unblinded researcher at Vrije Universiteit Brussel will regularly monitor data that are entered in Qualtrics. This researcher is independent from the funder of this study and has no competing interests.

#### Adverse event reporting and harms {22}

All adverse events (AEs) reported spontaneously by the patient or observed by the researcher will be recorded. Serious adverse events (SAEs) will be reported to the (local) principal investigators as soon as possible, who will be responsible for informing the ethics committee.

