### Intervention description {11a}

#### Control intervention: best medical treatment (BMT)

For each patient who is randomised to BMT, an optimal individual treatment plan will be developed by the treating physician. BMT can include oral medications (i.e. opioid, non-steroidal anti-inflammatory drug, antidepressant, anticonvulsant/antiepileptic and other analgesic therapies), nerve blocks, epidural adhesiolysis, neurotomies, physical and psychological rehabilitative therapy and/or chiropractic care [10, 11]. The protocol specifically excludes other invasive therapy, such as spinal surgery or implantation of an intrathecal drug delivery system. Starting from randomisation, BMT is actively managed and according to local clinical practice, where the treatment plan is optimised at each visit. The number of visits is according to standard clinical practice of the participating centres for PSPS-T2 patients. All interventions are documented in diaries for healthcare utilisation by the patients.

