#### Experimental intervention: subthreshold SCS

Participants randomly allocated to subthreshold SCS will undergo two surgical interventions to implant the neurostimulator. According to the Belgian reimbursement rules, all patients first need a SCS-trial period of 3 weeks with an external neurostimulator. After a successful trial according to Belgian legislation, i.e. pain reduction of at least 50% and reduction in medication use of at least 50%, the external neurostimulator will be replaced by an internal pulse generator (IPG). The implanting physician is free to choose the type of IPG that will be implanted.

SCS will be programmed at subthreshold stimulation, next to the conventional medical treatment that each patient will receive. As such, this intervention is similar to the BMT group with the addition of subthreshold SCS. Several subthreshold SCS stimulation types are provided such as high frequency SCS, burst SCS, high-dose SCS and differential target multiplexed SCS. For all stimulation types, patients do no longer feel paresthesia. Programming to subthreshold SCS will be performed on the day of IPG implantation.

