#### Provisions for post-trial care {30}

This study does not provide post-trial care. There is no anticipated harm for trial participation and consequently no compensation for anticipated harm.

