At baseline, all outcome measurements will be evaluated except for the impression of change and healthcare expenditure. Follow-up assessments will be performed one month after the start of the individualized best conservative treatment (BMT group) or 1 month after IPG implantation (SCS group), 6 months after start of the intervention (intermediate effects and primary endpoint) and 12 months (long-term effects) after intervention initiation. At 1 month and 12 months, outcome measurements can be completed without an additional hospital visit. Patients will receive a link towards the questionnaires to complete them online. At the 6-month follow-up, patients will complete the questionnaires at the hospital. After filling in the questionnaires at the 6-month follow-up visit, patients could change treatment groups (in both directions). This decision will be a shared decision between the patient and treating physician in case the randomised intervention did not provided enough pain relief. The cross-over will be mainly performed from BMT towards subthreshold SCS, according to study results obtained by Kumar et al. who evaluated standard SCS compared to BMT [10]. Figure 1 presents the project flowchart.

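### Adverse events are captured only if volunteered or observed, so non-serious events are likely to be under-recorded and recorded rates may not be comparable between arms

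*Protocol article*

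**What the plan says.** The section Adverse event reporting and harms {22} gives two routes by which an event enters the record: "All adverse events (AEs) reported spontaneously by the patient or observed by the researcher will be recorded". Serious events then go to the local principal investigators, who inform the ethics committee.

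Other sections determine how often those routes are open:

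- **SCS arm.** "Participants randomly allocated to subthreshold SCS will undergo two surgical interventions to implant the neurostimulator". A 3-week external trial comes between the operations, and programming takes place on the day the pulse generator is implanted. This is added to conventional care: "this intervention is similar to the BMT group with the addition of subthreshold SCS".
- **BMT arm.** "The number of visits is according to standard clinical practice of the participating centres for PSPS-T2 patients".
- **Assessment mode.** "At 1 month and 12 months, outcome measurements can be completed without an additional hospital visit". Patients receive a link, with completion in hospital for those without online access. Only the 6-month assessment is planned in hospital.
- **Data content.** The list under Data management {19} covers pain, disability, medication, quality of life, impression of change, work, self-management, healthcare expenditure, anxiety and depression. It names no adverse-event item.
- **Blinding.** Patients are asked not to tell the outcome assessor which intervention they received (Who will be blinded {17a}; Plans for assessment {18a}).

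**The concern.** Passive capture depends on a patient choosing to mention an event or on a researcher being there to see it. The planned conduct narrows both routes, and not necessarily to the same degree in the two arms. Minor wound, lead or device problems and medication side effects are the events most easily missed.

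At stake is the harm information that a reader will set beside the responder result. The protocol describes the study as a post-market clinical follow-up investigation that compares an added surgical treatment with medical management. If capture is incomplete, the event rates are too low. If capture is also unequal, a difference between arms may reflect who was asked or seen, and not who was harmed.

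**Working it through.** The plan gives no harm figure, so there is nothing to reproduce. The check sets the sections side by side and then illustrates the mechanism with assumed values.

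**1. Researcher observation.** Two of the three follow-ups (1 and 12 months) are normally online, so no researcher is present. Outside the assessments, the SCS arm has two operations and programming that the BMT arm lacks, while the number of BMT visits is left to each centre. No visit counts are given for either arm, so unequal contact is inferred from the intervention descriptions. The documents also do not say whether the treating physician counts as the researcher for this purpose.

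**2. Spontaneous report.** No adverse-event field is listed in the forms. At the 6-month hospital assessment, and at any other completion in hospital, patients are asked not to discuss their intervention with the assessor. That may discourage a patient from mentioning a wound or device problem, and it bears more on SCS patients.

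**3. Timing.** The SCS 1-month assessment is counted from pulse generator implantation (Outcomes {12}). The first operation and the 3-week trial therefore fall before the first post-baseline form. After 6 months patients may switch groups, and the protocol expects mainly BMT-to-SCS switches. The only scheduled assessment after those operations is the 12-month one, which is normally remote.

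**4. Direction.** Point 1 suggests fuller capture in SCS; point 2 suggests poorer capture in SCS. The documents do not settle which dominates.

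**5. Illustration.** Recorded risk = true risk × probability of capture. The 57 patients per arm come from Sample size {14}; every risk and capture rate below is an assumption.

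| True risk, SCS / BMT | Capture, SCS / BMT | Recorded, SCS / BMT | True difference | Recorded difference |
|---|---|---|---|---|
| 30% / 30% | 90% / 50% | 27% / 15% | 0 | +12 points |
| 30% / 30% | 50% / 90% | 15% / 27% | 0 | −12 points |
| 30% / 15% | 50% / 50% | 15% / 7.5% | +15 | +7.5 points |
| 30% / 15% | 50% / 90% | 15% / 13.5% | +15 | +1.5 points |
| 30% / 15% | 90% / 30% | 27% / 4.5% | +15 | +22.5 points |

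The first row corresponds to 57 × 0.27 = 15.4 against 57 × 0.15 = 8.6 patients with a recorded event, although the true risks are equal. The third row shows that equal but incomplete capture halves both rates and the difference.

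**The case against.** The strongest reply is that this is a short entry in a condensed article. Adverse-event forms, time points and tabulations commonly sit in the full protocol or analysis plan, and the list of collected data need not be exhaustive. That stands for forms and tabulations, and it means one can say only that no adverse-event item is listed, not that none exists. It does not remove the point, because the article states the capture rule itself, and the rule is passive.

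Partial safeguards also exist:

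- Hospital stays, treatments and consultations are self-reported by diary to 6 months and by questionnaire at 12 months.
- Medication is recorded at each visit.
- Patients receive follow-up phone calls.
- Serious events have their own reporting line and appear in the yearly ethics summary.

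These make it less likely that serious events are lost, and the point is therefore confined to non-serious ones. None is described as a means of capturing adverse events: the calls are for retention and the diary measures healthcare use.

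It is also fair that remote completion applies to both arms and so creates no imbalance by itself, and that BMT is actively managed at visits of its own.

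A reader might infer three stronger things that the documents do not support:

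- **That harms will certainly be under-counted, or biased in a known direction.** No capture rates or visit counts are given, and the features described pull in opposite directions.
- **That a planned comparison is invalid.** No between-arm test of harms is described, and no safety endpoint is among the stated outcomes.
- **That the remark under Provisions for post-trial care {30}, "There is no anticipated harm for trial participation", contradicts a surgical arm.** All participants must already be eligible for SCS implantation, so the remark can mean no harm beyond usual care. It is a separate matter of wording and says nothing about how events are ascertained.

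**Conclusion.** The point holds as an improvement to a stated method. Non-serious adverse events are likely to be under-recorded, and the chance of capture may differ by arm, so recorded event rates may not be comparable. Neither the direction nor the size of any bias follows from the documents; the 12-point shifts in the table show what assumed capture rates would do and are not estimates. The conclusion rests on two readings: that the harms section describes the whole capture route, and that the SCS procedures bring contacts beyond those of BMT. If the full protocol already contains a prompted question asked alike in both arms, the point falls away and the article's sentence only needs to say so. The primary responder analysis is unaffected.

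**What to change.** Add the same short adverse-event section to the existing Qualtrics forms at 1, 6 and 12 months in both arms: one open question and a brief list covering procedure or device events and medication events. Word the first form a patient completes so that it covers the whole period since randomisation, which brings in the first SCS operation and the trial stage. Send the answers to the unblinded researcher, who already monitors the Qualtrics data, and not to the blinded assessor, because the answers can reveal the allocation. Keep spontaneous reporting and the serious-event route as they are.

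The forms become slightly longer, and reported events need some follow-up by existing staff. Recruitment began in January 2022, so the change needs an amendment approved by the ethics committee. Events before and after it will be ascertained differently. The date of the change should be recorded and the difference reported with the harm results. No treatment or clinical rule changes.
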